### Outcome parameters

All outcome parameters are assessed via the parents’ entries in the ‘moma App’. For all outcome parameters, the difference from baseline to follow-up is measured and compared between the two groups.

The primary outcome parameter is the number of headache days per 12 weeks (84 days). Our hypothesis is that the reduction of headache days from baseline to follow-up will be at least 2 days larger for the group with interdisciplinary multimodal intervention in social pediatric centers (intervention group B) compared to the group with basic treatment in pediatric practices (intervention group A).

Secondary outcomes are:
Number of responders, defined as patients with a reduction of more than 50% of headache days per 12 weeks from baseline to follow-up;Headache intensity (averaged over headache days per 12 weeks);Number of days missed at school due to headache per 12 weeks;Number of days with cancelling of leisure activities due to headache per 12 weeks;Headache-related disability (PedMIDAS questionnaire) [18],assessed every 3 months;Quality of life (KINDL questionnaire, every 3 months) [19, 20];Number of days with intake of acute medication because of headache per 12 weeks.

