For the primary end point (number of headache days per 12 weeks) a mixed linear regression model is performed with the difference of headache days per 12 weeks from baseline to follow-up as dependent variable, the intervention in a social pediatric center (yes/no) as independent variable and random effects for the different social pediatric centers. Age, sex and headache frequency per 12 weeks at baseline are included as possible confounders. Quality of life (KINDL) and migraine related disability (PedMIDAS) at baseline are possible effect modifying elements and therefore integrated in the model as interaction effects. The significance level α is set at < 0.05. The same model is used for analysis of the secondary outcome parameters.

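### One linear change-score model is fixed for every secondary outcome; it does not suit the binary responder outcome, omits the own baseline for four of seven outcomes, and leaves headache intensity undefined in headache-free children

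*Protocol article*

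**What the plan says.** The Data analysis plan section of the protocol article defines one model in full, for the primary endpoint: "a mixed linear regression model is performed with the difference of headache days per 12 weeks from baseline to follow-up as dependent variable". Treatment at a social pediatric center is the explanatory variable, with random effects for centers. The covariates are then listed: "Age, sex and headache frequency per 12 weeks at baseline are included as possible confounders". Two further baseline scores enter differently: "Quality of life (KINDL) and migraine related disability (PedMIDAS) at baseline are possible effect modifying elements and therefore integrated in the model as interaction effects". Secondary outcomes get a single sentence: "The same model is used for analysis of the secondary outcome parameters".

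The Outcome parameters section is consistent with this. It says: "For all outcome parameters, the difference from baseline to follow-up is measured and compared between the two groups". Its seven secondary outcomes include "Number of responders, defined as patients with a reduction of more than 50% of headache days per 12 weeks from baseline to follow-up" and "Headache intensity (averaged over headache days per 12 weeks". The other five are missed school days, cancelled leisure days, PedMIDAS, KINDL and days with acute medication.

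**The concern.** A model written for the change in a count is carried over unchanged to outcomes of other kinds. For responders, the prescribed dependent variable does not exist, so the analyst must choose a model and an effect measure, possibly after seeing the data. For several other outcomes, the baseline value most closely tied to the outcome is not in the model, although the app collects it. For intensity, children who become entirely headache-free have no follow-up value. If they are left out, the arms are compared within a subset selected by a result that arises after randomisation, and the excluded share may differ by arm.

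**Working it through.** The article gives no figure for the secondary analyses, so there is none to reproduce. The check sets the stated model against each outcome and then sizes the consequences under assumptions.

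**Step 1: does the model fit each outcome?**

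| Secondary outcome | Difference score exists? | Own baseline in the model? |
|---|---|---|
| Responder status | No: binary, already a contrast with baseline | Baseline headache days, as covariate |
| Intensity on headache days | Only with at least one headache day in follow-up | No |
| Missed school days | Yes | No |
| Cancelled leisure days | Yes | No |
| Acute medication days | Yes | No |
| PedMIDAS | Yes | Yes, through a treatment interaction |
| KINDL | Yes | Yes, through a treatment interaction |

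The own-baseline gap therefore covers four of seven outcomes.

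**Step 2: responders.** A linear model on the 0/1 variable itself, not on a difference, can be fitted. This was simulated 100 times with 786 children (279 + 507), using assumed overdispersed headache counts, treatment and baseline headache days as predictors, and no clustering. Responder rates were about 40% (A) and 49% (B), and about 0.001% of fitted values fell outside 0 to 1. In that mid-range scenario a linear fit works as a risk-difference model. The article does not say that this is what it intends.

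**Step 3: precision lost without the own baseline.** Assume equal variance σ² at both times and correlation r.
- Change score with no baseline covariate: variance 2σ²(1 − r).
- Adjusted for own baseline: variance σ²(1 − r²).
- Proportional reduction: 1 − (1 − r²)/[2(1 − r)] = (1 − r)/2.

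Results:
- r = 0.3: 1.40 falls to 0.91, a reduction of 35%.
- r = 0.5: 1.00 falls to 0.75, a reduction of 25%.
- r = 0.7: 0.60 falls to 0.51, a reduction of 15%.

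These are upper bounds. The plan's model already contains baseline headache frequency, which should absorb part of the gain, especially for day counts that can arise only on headache days.

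**Step 4: PedMIDAS and KINDL.** With own baseline K and treatment T, the model contains b₁T + b₃(T × K). The treatment effect is b₁ + b₃K, so b₁ alone is the effect at K = 0 unless K is centred. The coefficient is conditional on the outcome's own starting score.

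**Step 5: children without an intensity value.** Baseline intensity always exists, because fewer than three baseline headache days leads to exclusion (Selection of sample; Data analysis plan). Follow-up has no such minimum. The imputation rules in the Data analysis plan are triggered by the share of diary days not filled in, and a complete diary without headache has no missing days. The share with none, for mean μ and negative binomial dispersion s, is:
- Poisson: exp(−μ). Negative binomial: [s/(s + μ)]^s.
- μ = 3: exp(−3) = 5%; s = 2 gives (2/5)² = 16%; s = 1 gives 1/4 = 25%.
- μ = 8: exp(−8) = 0.03%; s = 2 gives (2/10)² = 4%; s = 1 gives 1/9 = 11%.

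The share can differ by arm. Applying the hypothesised two-day difference to low-frequency children, Poisson means of 5 (A) and 3 (B) leave exp(−5) = 0.7% and exp(−3) = 5.0% headache-free. In the Step 2 simulation the shares were about 6% (A) and 8% (B). All means and dispersions are assumptions; the article gives none.

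**The case against.** A journal article condenses. It can be argued that the same model means the same structure, with each outcome and its baseline substituted, and that covariate lists and coding rules belong in the statistical analysis plan. That would carry weight had the article been silent. It instead fixes a rule, names the covariates, and says separately that a difference is taken for all outcomes.

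Other objections stand and limit the point:
- A reader might infer that the responder analysis cannot be run. A linear fit to the 0/1 status would run, and a sensible analyst would not difference it again. What stands is that neither the model nor the effect measure is stated.
- A reader might infer that no secondary outcome is adjusted for its own baseline. PedMIDAS and KINDL baselines are in the model, and responder status is served by baseline headache days.
- A reader might infer bias through regression to the mean. Under randomisation it acts in both arms; the cost is precision and uncorrected chance imbalance.
- A reader might infer that intensity is biased against the better arm. The article does not say that headache-free children are dropped, and the direction depends on what intensity change those children would have shown, on which it gives no data.
- Intensity when headache occurs is a legitimate clinical question. Scoring headache-free days as 0 mixes in frequency and overlaps with the primary outcome, so replacing the measure outright would be partly preference.

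**Conclusion.** The concern holds for the secondary outcomes, in three limited parts. First, the prescribed difference score does not exist for responders and no binary model is named. Second, four of seven outcomes lack their own baseline; the variance reduction forgone is at most about 15% to 35% for correlations of 0.7 to 0.3, less whatever baseline headache frequency already absorbs, and the randomised comparison is not biased by it. For PedMIDAS and KINDL the issue is instead a treatment coefficient conditional on the outcome's own baseline. Third, intensity is undefined in headache-free children and no stated rule covers them. Leaving them out would condition on a post-randomisation outcome, with bias of unknown direction, in perhaps 0-11% of children at a follow-up mean of 8 days or 5-25% at a mean of 3. Those shares rest on assumed distributions. This should be corrected, but it does not threaten the trial's main conclusion.

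**What to change.** Replace the single sentence on secondary outcomes with outcome-specific wording:
- **Responders:** mixed logistic regression or GEE, clustered by randomised region, reporting the odds ratio and the risk difference.
- **Continuous and count outcomes:** adjust each for its own baseline value as a main effect. Keep any interaction of treatment with the outcome's own baseline out of the main treatment-effect model; it can be reported separately as an effect-modification analysis.
- **Intensity:** label intensity on headache days as descriptive or conditional, and state how many children per arm have no value. Add a comparison of mean intensity over all observed days, with 0 on headache-free days, and note that it also reflects frequency.

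The cost is wording and a little programming. The app already collects every value needed, and no change to the sample size or the primary analysis follows.

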## Discussion

### Ethics, trial registration and data management

The study was approved by the local ethics committee at the Ludwig-Maximilians-University Munich (number 18–804, leading ethics committee) and approval was confirmed by all the other German ethics committees relevant for the study (*n* = 15). The study was retrospectively registered on 27 April 2021 in the WHO approved German Clinical Trials Register (number DRKS00016698). Data protection is established according to the European data protection regulation 2016/679. Only the data necessary for study conduction and analysis is obtained via the smartphone app (from the parents) and via the moma website (from the pediatricians in practice and from the social pediatric centers). The study data is saved on a dedicated server located at the University of Hof, Germany. Data is pseudonymized at the time point of collection using a hash-code based on the patient’s name and birth date. This hash-code is only used to link data from the same patients on the server. It does not allow back-tracing of the patient’s name or birth date. The data will be stored for ten years.

### Importance and dissemination

Migraine is a prevalent and disabling disease in childhood. Therapeutic options are scarce or not well tolerated by the children or their parents. Studies about the efficacy of non-invasive, non-pharmaceutical interdisciplinary treatment in young children with focus on the association of muscle tenderness and migraine do not exist so far. Hence, the presented intervention study is of high interest not only for the young patients but also for the pediatric and scientific communities as well as for the health systems worldwide. Therefore, we plan to publish the results of the multimodal intervention study in international scientific medical journals with a high distribution rate among pediatricians and neuropediatricians. As the topic is also relevant for health politics, the results will also be published at the homepages or newsletters of relevant medical professional societies. The study outcomes will also be discussed at national and international congresses for (Neuro-) Pediatrics.

### Strengths and limitations

The first strength of the study is the possible positive impact of the results for the participating child with migraine and its family. The second strength is the randomized controlled design with planned nationwide participation of pediatricians in practice and of interdisciplinary social pediatric centers. The third strength is the clinical and political importance of the study subject: interdisciplinary intervention programs for children with migraine are mandated but efficacy studies in this age group are lacking.

A limitation pertains to health system differences between countries, reducing generalizability of study results. The realization of study might be cumbersome because of challenges for pediatric practices related to the current COVID-19 pandemic.

## Data Availability

The datasets used and analysed during the current study are available from the corresponding author on reasonable request.

## Abbreviations

α: Significance level
App: Smartphone application
approx: Approximately
COVID-19: Coronavirus disease 2019
G-BA: Gemeinsamer Bundesausschuss = Federal Joint Committee
ICC: Intra-class correlation coefficient
ICD-10: International Classification of Diseases 10th revision
ICHD-3: International Classification of Headache Disorders 3rd edition
IQ: Intelligence quotient
KINDL: Name of a German tool for assessing pediatric quality of life
LOCF: Last observation carried forward
moma: Modules on migraine activity = name of the study
n: Number
NSAID: Nonsteroidal antiinflammatory drugs
PedMIDAS: Pediatric Migraine Disability Assessment Score
TCC: Trigemino-cervical complex
WHO: World Health Organization
